### 3.2 Rationale

#### 3.2.1 Efficacy and Pharmacology Study of Atorvastatin

##### 1) Efficacy:

In a multi-center, placebo-controlled, dose-finding study in hyperlipidemia patients, it was confirmed that total cholesterol, LDL-C, Apo B, and triglyceride decreased significantly when atorvastatin is administered at a single dose (placebo, 10, 20, 40, and 80 mg) for  $\geq 6$  weeks.

##### 2) Pharmacology:

- Rhabdomyosarcoma and fibrosarcoma were observed in the muscles of rats administered a high dose of atorvastatin, but the dose was equivalent to approximately 16 times the exposure with oral administration of 80 mg to humans.
- In the high dose groups of male and female mice, an increase in liver adenomas was observed, but the dose was equivalent to approximately 6 times the exposure with oral administration of 80 mg to humans.
- The results of the genetic toxicity test using microorganisms and the micronucleus test using mice were confirmed to be negative.
- When atorvastatin 100 mg/kg/day (approximately 16 times the exposure with oral administration of 80 mg to humans) was administered to rats for 3 months, azoospermia was found in 2 out of 10 rats. When the same

dose was administered to rats for 11 weeks, the movement of sperms and the concentration of sperm heads decreased and the number of abnormal sperms increased.

- When atorvastatin 10, 40, and 120 mg/kg were administered to dogs for 2 years, there was no histopathological AEs in semen parameters and reproductive organs.

### 3.2.2 Mechanism of Action of Atorvastatin

Atorvastatin inhibits HMG-CoA reductase, which is the enzyme that acts on the process of converting HMG-CoA into mevalonic acid, in the rate-limiting step of cholesterol synthesis. This reduces the production of cholesterol in the liver cells, which causes a decreased amount of cholesterol within the cells. As a result, the expression of LDL receptors on the liver cell surface is increased, which in turn greatly reduces cholesterol in the blood and lower the concentration of serum cholesterol.

### 3.3 Assessment of Benefits

1. Reduced risk of the following cardiovascular diseases
  - 1) For adult patients with multiple risk factors for coronary artery heart disease ( $\geq 55$  years of age, smoking, hypertension, low HDL-cholesterol, family history of premature coronary artery heart disease, etc.) in spite of no clinical evidence of coronary artery heart disease,
    - (1) Reduced risk of myocardial infarction
    - (2) Reduced risk of stroke
    - (3) Reduced risk of revascularization and chronic stable angina
  - 2) For patients with type 2 diabetes mellitus with multiple risk factors of coronary artery heart disease (retinopathy, albuminuria, smoking, hypertension, etc.) in spite of no clinical evidence of coronary artery heart disease,
    - (1) Reduced risk of myocardial infarction
    - (2) Reduced risk of stroke
  - 3) For adult patients with clinical evidence of coronary artery heart disease,
    - (1) Reduced risk of nonfatal myocardial infarction
    - (2) Reduced risk of fatal and nonfatal stroke
    - (3) Reduced risk of revascularization
    - (4) Reduced risk of hospitalization for congestive heart failure
    - (5) Reduced risk of angina pectoris
2. Hyperlipidemia
  - 1) As an adjunct to diet to reduce elevated total cholesterol, LDL cholesterol, Apo B, and triglyceride levels and to increase HDL cholesterol in adult patients with primary hypercholesterolemia (heterozygous familial and nonfamilial) and mixed dyslipidemia (Fredrickson Types IIa and IIb);
  - 2) For the treatment of adult patients with primary dysbetalipoproteinemia (Fredrickson Type III) who do not respond adequately to diet
  - 3) As an adjunct to diet for the treatment of adult patients with elevated serum TG levels (Fredrickson Type IV)
  - 4) To reduce total cholesterol and LDL cholesterol in patients with homozygous familial hypercholesterolemia as an adjunct to other lip-lowering treatments (e.g., LDL-apheresis) or if such treatments are unavailable

### 3.4 Rationale for the Selection of Doses

The investigational products (IPs) of this study have been approved by the Ministry of Food and Drug Safety (MFDS). Doses of Lipilou approved by the MFDS are shown below.

| Item         | Republic of Korea     |
|--------------|-----------------------|
| Strength     | 10, 20, 40, and 80 mg |
| Maximum dose | 80 mg                 |

This study will use 10 mg and 20 mg of Lipilou among the doses approved by the MFDS to compare and evaluate the efficacy and safety.

## 4 Study Objective

Only the subjects who meet the inclusion/exclusion criteria will be randomized to either 1 tablet of the study drug (Lipilou 20 mg) or 1 tablet of the control drug (Lipilou 10 mg) and take the doses for 12 weeks for the following objectives.

- A. Primary objective:  
To evaluate the percent change from baseline in LDL-C at Week 12
- B. Secondary objectives:
  - ① To evaluate the percent changes from baseline in lipid parameters at Week 12
  - ② To evaluate the changes from baseline in HbA1c and glucose at Week 12
  - ③ To evaluate the percentage of subjects achieving the target LDL-C by risk group
  - ④ To evaluate the percentage of subjects achieving the target non-HDL-C by risk group
  - ⑤ To evaluate the safety based on AEs, vital signs, laboratory tests, etc.
- C. Exploratory objective:  
To evaluate pharmacoeconomics of Lipilou 20 mg and 10 mg at Week 12 from baseline

## 5 Study Population

### 5.1 Number of Subjects

248 subjects (124 subjects per group)

### 5.2 Inclusion Criteria

1. Adults aged  $\geq 19$  years
2. Patients in the following high-risk group or above as per the Korean Guidelines for the Management of Dyslipidemia (Committee for Guidelines for Management of Dyslipidemia, 2015, 3rd edition)  
High-risk group:
  - 1) Carotid artery disease (confirmed carotid artery stenosis of  $> 50\%$ )
  - 2) Abdominal aneurysm
  - 3) Diabetes mellitus
 Very high-risk group:
  - 1) Coronary artery disease
  - 2) Ischemic stroke
  - 3) Transient cerebral ischemic attack
  - 4) Peripheral vascular disease
3. At Visit 1 (screening),
  - 1) If a subject is taking a lipid lowering agent, the subject will have a wash out period only if LDL-C is  $\leq 250$  mg/dl and TG is  $\leq 500$  mg/dl  
(Subjects who are taking fibrates will have a wash out period of  $\geq 8$  weeks prior to Visit 2, and subjects who are taking agents other than fibrates will have a wash out period of  $\geq 4$  weeks prior to Visit 2)
  - 2) If a subject is drug-naïve or has not taken fibrates for  $\geq 8$  weeks or agents other than fibrates for  $\geq 4$  weeks, then subjects who meet the following criteria will proceed with Visit 3 and be randomized without a wash out (Visit 2 will be skipped).
    - ① High-risk group: LDL-C  $\geq 100$  mg/dl and TG  $\leq 500$  mg/dl
    - ② Very high-risk group: LDL-C  $\geq 70$  mg/dl and TG  $\leq 500$  mg/dl
4. If a subject (who had a wash out period at Visit 1) has the following test results at Visit 2, the subject will proceed with Visit 3 and be randomized.
  - ① High-risk group: LDL-C  $\geq 100$  mg/dl and TG  $\leq 500$  mg/dl
  - ② Very high-risk group: LDL-C  $\geq 70$  mg/dl and TG  $\leq 500$  mg/dl

### 5.3 Exclusion Criteria

1. Uncontrolled following diseases
  - Diabetes mellitus (HbA1c  $> 9\%$  at screening)
  - Hypertension (systolic blood pressure  $\geq 180$  mmHg or diastolic blood pressure  $\geq 110$  mmHg at screening)
  - Thyroid dysfunction (TSH  $\geq 1.5$  x upper limit of normal [ULN] at screening)
2. Severe renal or hepatic impairment, active liver diseases, or serum creatinine, AST, or ALT  $\geq 2$  x ULN
3. Myopathy such as musculoskeletal disorders or rhabdomyolysis, or CPK (CK) level  $\geq 2$  x ULN
4. Medical or surgical conditions that may affect absorption, distribution, metabolism, and excretion of the investigational product (IP)
  - History of major gastrointestinal surgeries including gastrectomy, gastrointestinal bypass graft, and gastrointestinal anastomosis (excluding simple appendectomy and hernia repair)
  - History of active inflammatory bowel syndrome within the last 12 months
  - Pancreatic dysfunction (e.g., cholestasis) such as Crohn's disease and pancreatitis currently requiring treatment, or gastrointestinal/rectal bleeding
5. History of hypersensitivity or allergies to any ingredient of the IP
6. History of drug or alcohol abuse within the last 6 months
7. Patients who do not agree to use contraception (Women who have been amenorrheic for at least 12 months will be considered to be postmenopausal)
8. Patients who took other investigational agent within 30 days prior to the first dose of the IP
9. Patients who are difficult to stop drugs that affect the lipid levels after informed consent or require administration of other hypercholesterolemia drugs during the study
10. Patients who require administration of any prohibited concomitant medication specified in this protocol during participation in the study
11. Hereditary disorders such as galactose intolerance, Lapp lactase deficiency, or glucose-galactose malabsorption because this drug contains lactose
12. Inability to participate in the study by law or at the judgment of the investigator

## 6 Study Design

### 6.1 Study Duration

To be completed within 24 months from the date of the IRB approval

### 6.2 Group Assignment

#### 6.2.1 Randomization

In this study, only the subjects who meet the inclusion criteria will be randomized in a 1:1 ratio. In order to assign subjects to each group in balance, a restricted block randomization method that include study site and risk group result as strata, will be applied, and the block size will be selected among multiples of 2 (e.g., 2, 4, 6, etc.) A randomization table will be created by the biostatistician in charge of randomization using the IWRS, SAS, etc. In order to randomize subjects who meet the inclusion/exclusion criteria and are considered to be eligible to participate in the study based on the risk group information, a stratification variable, randomization will be automatically performed by the IWRS, and the randomization result can be found on the electronic case report form (e-CRF).

When conducting a multi-center study, it is important to standardize the study procedures according to the shared protocol so that the study can be conducted in a similar manner at all sites. Thus, the distribution of subjects should be the same among the study sites to assume that the therapeutic effect would be the same among the study sites.

Once data required to assign an allocation number (AN) are entered on the e-CRF, subjects will be randomized to either the study group or control group by the IWRS. If an AN is erroneously assigned due to errors in the data entry, etc., the already assigned AN cannot be corrected, and the study will proceed as randomized. Subjects enrolled afterwards will be automatically assigned an AN in the order of numbers set in the system.

### 6.3 Study Flow Diagram

[figure not shown]

## **7 Criteria for Completion of Study, Termination of Study, and Early Discontinuation**

### **7.1 Criteria for Completion of Study**

Subjects who complete all scheduled activities including protocol-specific treatments, tests, and visits will be defined as having completed the study.

### **7.2 Criteria for Early Discontinuation**

If a subject meets any of the following, the subject may be terminated from the study early. In principle, in case of early discontinuation, all tests scheduled for the final visit (Visit 4) will be performed preferably at the last visit date. All abnormalities found in the physical examination and laboratory test results of the subject will be followed up, if possible.

1. A subject is considered difficult to receive further doses of the IP due to AEs
2. A subject is not cooperative during the study
3. A subject or legally acceptable representative voluntarily withdraws consent to continue participation in the study
4. A major protocol deviation is found
5. A subject becomes pregnant during the study
6. A subject is considered ineligible to participate in the study by the investigator for other reasons
7. A subject is lost to follow-up

A subject who experiences any unexpected change during the study must immediately notify the investigator by phone, etc. and be examined by the investigator, if necessary. If an undesirable change occurs to a subject, the investigator may exclude the subject from the study at any time by the subject's voluntary decision or at the judgment of the investigator.

### **7.3 Criteria for Termination of Study**

If a subject shows significant toxicity that is unacceptable to the investigator, the study may be completely terminated for the subject.

## 8 Identity and Management of the Investigational Products

### 8.1 Identity of the Investigational Products

#### 8.1.1 Study Drug: Lipilou Tablet 20 mg

- 1) Generic name: Atorvastatin calcium anhydrous
- 2) Product name: Lipilou tablet 20 mg
- 3) Drug substance and its content: Atorvastatin calcium anhydrous 20.720 mg
- 4) Appearance and dosage form: White, round-shaped film-coated tablet
- 5) Storage condition: Store in a tight container at room temperature (1 - 30 °C)

#### 8.1.2 Control Drug: Lipilou Tablet 10 mg

- 1) Generic name: Atorvastatin calcium anhydrous
- 2) Product name: Lipilou tablet 10 mg
- 3) Drug substance and its content: Atorvastatin calcium anhydrous 10.360 mg
- 4) Appearance and dosage form: White, round-shaped film-coated tablet
- 5) Storage condition: Store in a tight container at room temperature (1 - 30 °C)

### 8.2 Labeling

Chong Kun Dang Pharmaceutical Corp. will label the IPs manufactured (or purchased) with a label as shown below (refer to Annex 4-2 [Paragraph 8.4] of the Regulation on the Safety of Pharmaceuticals, etc. and Paragraph 7.7 of the Good Manufacturing Practice for Medicinal Products).

|                                                                                                                                                                                                                                                                                                                                                                                                                                 |                           |
|---------------------------------------------------------------------------------------------------------------------------------------------------------------------------------------------------------------------------------------------------------------------------------------------------------------------------------------------------------------------------------------------------------------------------------|---------------------------|
| IP No.                                                                                                                                                                                                                                                                                                                                                                                                                          | [Protocol No: 124HL17003] |
| Investigational Product                                                                                                                                                                                                                                                                                                                                                                                                         |                           |
| 
 
1. Product name:
 
2. Batch number:
 
3. Expiry date:
 
4. Storage condition:
 
5. Company name, address, and contact information of the IND holder: Chong Kun Dang Pharmaceutical Corp.,
[name]/[contact]
 
6. Keep away from children.
 
7. Instructions for use:
 
 |                           |
| 
Instructions for use: Take 1 tablet once daily preferably at the same time (in the morning) of the day
                                                                                                                                                                                                                                                                                                                   |                           |

### 8.3 Packaging

The IPs will be manufactured and packaged by Chong Kun Dang Pharmaceutical Corp. and supplied to the study pharmacists at the study sites in accordance with the 'Regulation on the Safety of Pharmaceuticals, etc.' This study will be an open-label study. The IPs provided during the study will be packaged in a tight container and provided in an open-label manner.

### 8.4 Accountability

Chong Kun Dang Pharmaceutical Corp. will supply the packaged IPs to the study pharmacists at the study sites. The study pharmacists at the study sites will inspect the IPs upon receipt and record the relevant information in an IP accountability log. Chong Kun Dang Pharmaceutical Corp. should make sure that the IPs are adequately supplied in a timely manner through active communication with the study pharmacists and periodic monitoring.

The pharmacists who manage the IPs (hereinafter, 'study pharmacists') are responsible for receipt, storage, preparation, management, and return of the IPs.

The study pharmacists will acknowledge the receipt and quantity of the IPs in writing by signing and manage them properly. They should ensure that the IPs are administered to the subjects in accordance with the protocol, and accurately record the management of all the IPs provided to each subject.

Once data required to assign an IP number (item number or product number) are entered on the e-CRF, an IP number will be automatically assigned by the IWRS. If an IP number is erroneously assigned due to errors in the data entry, the assignment may be canceled as long as the IP has not been dispensed to the subjects, and an appropriate preventive training will be provided, if necessary.

### 8.5 Returns and Destruction

Unused IPs will be stored until the sponsor makes a decision on destruction or collection. Upon the end of study, all unused IPs, used/unused containers, labels, and copies of the IP management records will be submitted to the responsible monitor.

In principle, unused IPs or IPs returned by the subjects will be collected and destroyed by Chong Kun Dang Pharmaceutical Corp., and detailed procedures will follow the company's SOP.

## 9 Study Method, Administration Schedule, Etc.

### 9.1 Administration and Treatment Schedule

#### 9.1.1 Screening and Wash Out Period: from Weeks -9 to -5

If a subject is taking a lipid lowering agent at screening, the subject will have a wash out period as follows only if LDL-C is  $\leq 250$  mg/dl and TG is  $\leq 500$  mg/dl.

- For fibrates, subjects will have a wash out period of  $\geq 8$  weeks.
- For agents other than fibrates, subjects will have a wash out period of  $\geq 4$  weeks.

If a subject drug-naïve or has not taken fibrates for  $\geq 8$  weeks or agents other than fibrates for  $\geq 4$  weeks at screening, the subject will proceed with Visit 3 and be randomized without a wash out according to the following criteria (Visit 2 will be skipped).

- High-risk group: LDL-C  $\geq 100$  mg/dl and TG  $\leq 500$  mg/dl
- Very high-risk group: LDL-C  $\geq 70$  mg/dl and TG  $\leq 500$  mg/dl

#### 9.1.2 Run-in Period: Week -1

Subjects with LDL-C  $\geq 100$  mg/dl and TG  $\leq 500$  mg/dl in the high-risk group and subjects with LDL-C  $\geq 70$  mg/dl and TG  $\leq 500$  mg/dl in the very high-risk group after the wash out will be randomized at Visit 3 and dispensed with the IP.

If drug-naïve subjects or subjects who have not taken fibrates for  $\geq 8$  weeks or agents other than fibrates for  $\geq 4$  weeks at screening meet the inclusion/exclusion criteria without a wash out period, Visit 2 will be skipped and randomization will be performed at Visit 3 to dispense the IPs.

#### 9.1.3 Treatment period: Weeks 0 to 12

Subjects will take 1 tablet of either Lipilou 10 mg or Lipilou 20 mg as randomized once daily for 12 weeks and are recommended to take the drug preferably at the same time (in the morning) of the day.

At Visit 4 (Week 12; out-patient visit), subjects should visit the site without having taken the IP and complete all tests scheduled for that visit. If a subject took the IP, the subject should revisit to have the scheduled tests.

### 9.2 Concomitant Medications

Drugs that are not specified in Section 9.3 Prohibited Medications and are considered to have no effect on the interpretation of the study results may be taken or administered at the judgment of the investigator, considering the subject's condition. Concomitant medications taken or administered during the study must be recorded on the e-CRF.

### 9.3 Prohibited Medications

The following medications will be prohibited during the study:

#### 1) Drugs that lower lipid levels

- ① Statins, fibrates, ezetimibe, bile acid sequestrants, niacin, anti-obesity drugs, systemic steroids, fish oil, colestine products, fiber-based laxatives, phytosterol margarines, etc. (topical/external steroids may be concomitantly used)

#### 2) Drugs that increase the frequency of side effects or cause abnormal plasma concentration when used concomitantly

- ① CYP3A4 inhibitors (cyclosporine, macrolide antibiotics, azole antifungals, and protease inhibitors): erythromycin, atazanavir, clarithromycin, indinavir, itraconazole, ketoconazole, nefazodone, telaprevir, tipranovir+ritonavir combination, lopinavir+ritonavir combination, saquinavir+ritonavir combination, fosamprenavir, darunavir+ritonavir combination, fosamprenavir+ritonavir combination, etc.
- ② Drugs that affect thyroid function (administration of anti-thyroid agents or thyroxine: subjects on replacement therapy are not applicable)
- ③ CYP3A4 inducers: rifampin, carbamazepine, efavirenz, etc.
- ④ P-glycoprotein inhibitors: cyclosporine, verapamil, and diltiazem
- ⑤ Colestipol
- ⑥ Oral contraceptives containing norethisterone and ethinyl estradiol
- ⑦ Antacids
- ⑧ Grapefruit juice: intake of 1.2 L or more per day is not allowed
- ⑨ Nicotinic acid
- ⑩ Gemfibrozil

#### 3) Other investigational agents

If criteria for temporary or stable use for each agent are met, the following drugs may be used concomitantly. For temporary use, a short-term use within 7 days is allowed, but they must not be taken or administered within 4 days

prior to a scheduled visit. For stable use, they may be taken or administered as long as their dosage is not changed from the time of informed consent until the end of the study.

- Drugs allowed for temporary use: systemic steroids and antacids
- Drugs allowed for stable use: P-glycoprotein inhibitors, oral contraceptives, antacids, and drugs that affect thyroid function (administration of anti-thyroid agents or thyroxin: subjects on replacement therapy are not applicable)

Subjects who sign the informed consent form should be trained to follow guidelines on TLC for the treatment of hypercholesterolemia, as much as possible.

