| 2 | 
Visit window and duration of discontinuation of lipid lowering agents
 
① Visit 1: Subjects who meet the inclusion/exclusion criteria and require a wash out will have a wash out period as follows.
 
 
For fibrates, subjects will have a wash out period of <math>\geq 8</math> weeks prior to Visit 2
 
For agents other than fibrates, subjects will have a wash out period of <math>\geq 4</math> weeks prior to Visit 2
 
 
② Visit 2: After completion of the wash out, subjects will have tests scheduled for Visit 2.
 
③ Visit 3: Subjects who meet the inclusion/exclusion criteria at Visit 2 (or subjects who are drug-naïve at Visit 1 or have not taken fibrates for <math>\geq 8</math> weeks or agents other than fibrates for <math>\geq 4</math> weeks at screening and meet the inclusion/exclusion criteria) will be dispensed with the IP and take the IP starting from the day of Visit 3.
 
If drug-naïve subjects or subjects who have not taken fibrates for <math>\geq 8</math> weeks or agents other than fibrates for <math>\geq 4</math> weeks at screening meet the inclusion/exclusion criteria without a wash out period, Visit 2 will be skipped and randomization will be performed at Visit 3 to dispense the IPs.
 
④ Visit 4: The allowed visit window will be 4 days (<math>\pm 4</math> days) before and after the date specified relative to Visit 3.
 |

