| 8 | All concomitant medications within 4 weeks from the date of informed consent will be examined. During the study, any change in concomitant medications since last visit will be examined in detail at every visit and administration of prohibited concomitant medications will be checked for.                                                                                                                                                                                                                                                                                                                                                                                                                                                                                                                                                                                                                                                                                                                                                                                                                                                                                                                                                                                                                                                                                                                                                                                    |

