Subjects should have laboratory tests in a fasting state (fasting for at least 9 hours) to exclude food effect. Subjects who are not in a fasting state should revisit to have the laboratory tests.  
\* One re-test is allowed. If a re-test is performed, the run-in period may last until Week -2 (Day -14).
  - ⑤ Assessment of AEs and concomitant medications  
AEs that occurred and concomitant medications taken since last visit will be examined.
  - ⑥ Training on TLC:  
Subjects will be checked if they have been implementing TLC for the treatment of hypercholesterolemia since last visit.
  - ⑦ Discontinuation of lipid lowering agents  
Subjects will continue to stop using antihyperlipidemic agents.
  - ⑧ Assessment of inclusion/exclusion criteria
- 3) Visit 3: Treatment period (Week 0)**
- ① Pregnancy test  
A pregnancy test (urine hCG) will be performed only for women of childbearing potential who are not postmenopausal (who have been amenorrheic for at least 12 months) or are not surgically sterile, and appropriate contraceptive methods will be used throughout the study.  
\* At Visit 3, pregnancy will be verified immediately using a pregnancy test kit provided by the central lab and the result will be recorded in the source document.
  - ② AN assignment  
Subjects who finally meet the inclusion/exclusion criteria will be randomized by the IWRS. An AN is a 5-digit number, and the first 2 digits will represent the site number and the rest 3 digits will represent the order of randomization.  
For example, the 5th subject to be assigned an AN at site number 8 will be assigned 'AN08-005'.
  - ③ Dispensing of IPs  
The IPs to be taken for 12 weeks (doses for 100 days with overage for 16 days included) will be dispensed, and subjects will be recommended to take 1 tablet of the IP once daily at the same time of the day and will take the drug starting from the day of dispensing. Subjects will be instructed not to take the IP on the day of the next visit (Visit 4), and if they took the IP, they should revisit to have the scheduled tests. Subjects will be instructed to bring unused IPs when visiting the site.
  - ④ Assessment of AEs and concomitant medications  
AEs that occurred and concomitant medications taken since last visit will be examined.
  - ⑤ Training on TLC:  
Subjects will be checked if they have been implementing TLC for the treatment of hypercholesterolemia since last visit.
- 4) Visit 4: End of study visit (Week 12)**
- ① Vital signs  

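### Section 9.3 both prohibits cyclosporine (as a CYP3A4 inhibitor) and permits it at a stable dose (as a P-glycoprotein inhibitor)

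*Protocol*

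**What the plan says.** Section 9.3 opens with a general rule: "The following medications will be prohibited during the study". Item 2) of the list covers drugs that, in the Protocol's own description, raise the frequency of side effects or disturb plasma concentrations. Cyclosporine appears there twice:

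- Item 2)① begins "CYP3A4 inhibitors (cyclosporine, macrolide antibiotics, azole antifungals, and protease inhibitors" and goes on to name individual agents, ending in an open 'etc.'.
- Item 2)④ reads "P-glycoprotein inhibitors: cyclosporine, verapamil, and diltiazem", a closed list of three.

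The section ends with two sets of exceptions. Short temporary use is allowed for systemic steroids and antacids. Use at a dose unchanged from consent to the end of the study is allowed for a second set: "Drugs allowed for stable use: P-glycoprotein inhibitors, oral contraceptives, antacids, and drugs that affect thyroid function".

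Two other provisions depend on this list. Section 5.3, item 10, excludes "Patients who require administration of any prohibited concomitant medication specified in this protocol during participation in the study". Note 8 to the Summary of Study Schedule says that at every visit "administration of prohibited concomitant medications will be checked for".

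**The concern.** A drug needs one status. As written, a site can reach opposite answers for a patient on long-term cyclosporine, depending on which entry it reads. Item ① has no exception and bars the patient. Item ④ together with the stable-use line admits the patient, provided the dose does not change.

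Three things depend on the answer:

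- **Eligibility.** Exclusion criterion 10 applies or does not apply.
- **Conduct.** It is undetermined whether cyclosporine use is a deviation at all. A major deviation can lead to early discontinuation (Section 7.2, item 4) and to removal from the PP Set (Section 11.1.2).
- **Safety.** A subject whom item ① bars could be enrolled in either dose arm. Section 10.1 hands over the whole supply at Visit 3: "The IPs to be taken for 12 weeks (doses for 100 days with overage for 16 days included) will be dispensed". No visit or laboratory test, CPK included, is scheduled again until Visit 4.

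**Working it through.** The main check is a comparison of text. The Protocol states no figure on this point that could be reproduced.

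**Step 1: status of each route for cyclosporine at a stable dose**

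| Entry in 9.3, item 2) | Cyclosporine named? | On temporary-use list? | On stable-use list? | Result |
|---|---|---|---|---|
| ① CYP3A4 inhibitors | Yes | No | No | Prohibited |
| ④ P-glycoprotein inhibitors | Yes | No | Yes, whole class | Permitted |

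**Step 2: is there a tie-break?** Section 9.3 states no order of precedence and makes no carve-out for cyclosporine. Being on the prohibited list cannot settle the matter either. Every group on the stable-use line is itself prohibited in item 2) (②, ④, ⑥ and ⑦), so the line exists to lift prohibitions.

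**Step 3: how many named drugs are affected?** Among the named drugs, take those in a class with a stable-use exception (②, ④, ⑥, ⑦) and look for them in a class without one. Verapamil and diltiazem are named only under ④. Cyclosporine is the only drug named on both sides, so one drug is affected.

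**Step 4: time on treatment before the next scheduled laboratory test, on the permissive reading.** Visit 4 is at Day 84, and note 2 to the Summary of Study Schedule says "The allowed visit window will be 4 days" either side.

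- From the first dose at Visit 3 (Day 0): 84 − 4 = 80 to 84 + 4 = 88 days.
- From the Visit 2 test (Day −7 to −3): 3 + 80 = 83 to 7 + 88 = 95 days.
- If a re-test extends the run-in to Day −14: at most 14 + 88 = 102 days. This counts from the first test, so it overstates the gap for anything repeated later.
- For subjects who skip Visit 2, the last scheduled test is at Visit 1. The nominal Visit 1 window (Day −63 to −35) gives 35 + 80 = 115 to 63 + 88 = 151 days.

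The 80 to 88 days on treatment apply to every subject. The wording in Section 9.3 does not create that interval. It decides whether a subject on cyclosporine goes through it.

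**The case against.** The strongest reply is that the items in Section 9.3 are separate grounds for prohibition and therefore cumulative. The stable-use line names classes, so it lifts only the ground in ④. Ground ① is untouched, and cyclosporine is the first drug it names. On this reading cyclosporine stays barred, and the exception still has content because it covers verapamil and diltiazem. This is the sensible conservative reading, and many sites would adopt it. But the Protocol does not state it. The exception paragraph says without qualification that the listed drugs may be used, and cyclosporine is one of only three drugs that make up the exempted class. A site that allowed it would be following the text.

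A second reply is that the day counts measure the visit schedule and not this defect. That is correct, and the finding does not rest on them.

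A third is that harm is unlikely. It needs a candidate on cyclosporine, a site that overlooks item ①, and an investigator who sees no concern. Exclusions 2 and 12 and the option of unscheduled visits give some protection. These points narrow the effect and support a minor rating, but they do not resolve the wording.

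Last, the sponsor's intent is unknown, and it could choose to permit cyclosporine. That is fair. Either choice would remove the conflict, but prohibition fits the Protocol's own safety reason for item ①.

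**Conclusion.** The concern holds. Section 9.3 assigns cyclosporine at a stable dose two incompatible statuses and gives no rule for choosing between them, and exclusion criterion 10 carries the conflict into eligibility.

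Severity is minor. One named drug is involved. The document gives no count of affected patients; that the number is very small is an assumption. On that assumption the primary LDL-C comparison is essentially unaffected. What remains is inconsistent enrolment between sites, uncertainty over what counts as a deviation, and an avoidable safety exposure for any such subject.

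**What to change.** In the stable-use line of Section 9.3, replace the unqualified class with *P-glycoprotein inhibitors other than cyclosporine (i.e., verapamil and diltiazem)* and leave the rest of the line as it is. Cyclosporine then stays prohibited under item 2)①, exclusion criterion 10 applies to it, and the existing permission for the other two drugs is unchanged. If the sponsor instead means to allow cyclosporine, it should say so expressly in item ① and give the safety reasoning.

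The cost is one wording change and a letter to sites. Design, endpoints, analysis and sample size stay as they are. The drawback is that the rare patient on stable cyclosporine cannot enrol, which item ① already implies.
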